### 2.12. Statistical Analysis

Standard analysis methods for randomized controlled trials will be employed. The distribution of the data will be assessed with the Shapiro-Wilk test. Between-group comparisons at baseline will be performed with Student’s t-test, the Mann-Whitney test, or the chi-squared test according to the nature and distribution of the data. Between-group differences in all outcomes according to the trial hypotheses will be tested with Student’s t-test or the Mann-Whitney U test as appropriate. Within-group outcomes will be assessed using the paired-samples t-test or the Wilcoxon signed-rank test. In case of baseline differences between groups, appropriate adjustment measures (e.g., analysis of covariance) will be carried out. An intention-to-treat analysis will be used, with missing values replaced using the multiple imputation procedure (although all efforts will be made to minimize their incidence). A sensitivity analysis (e.g., per protocol) will also be performed to test the stability of the conclusions.

Moreover, Kaplan–Meier analysis and Cox regression will be used to model the incidence rates of long-term clinical outcomes (hospitalization and death). Subgroup analyses will be scheduled to determine the impact of the findings in smaller populations (e.g., to determine gender differences [40], etc.). Kaplan-Meier estimates of the distribution of times from the beginning of rehabilitation to the clinical events and a log-rank test for trend will be used to compare the curves of the patient groups. A p value < 0.05 will be considered significant. Data will be analyzed using SPSS 21.0 (IBM, Armonk, NY, USA) and MedCalc statistical software (version 19.8 and later, MedCalc Software bvba, Ostend, Belgium).

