### 2.5. Randomization and Blinding

A team member responsible for the enrollment will generate the allocation sequence on a personal password-protected computer, with access granted only to the research coordinator and the administrator. Then, in order to prevent selection bias, patients will be randomized between the two groups through a computerized randomization stratification approach by an external administrator not involved in the trial. Participants will be stratified by their degree of PAD severity (ankle-brachial index [ABI] > or <0.5) and the presence of diabetes. The randomization scheme (1:1 ratio) will be structured in permuted blocks of 8 to ensure a similar number of participants between groups. Ultimately, each of the subjects will be assigned to receive one of two treatments: TiTo-SHB (experimental group) or walking advice as an active control (C). The participants cannot be blinded to the two interventions, as the training protocol is detailed in the information form. Once randomized, a participant will not be transferred to the other treatment group for any reason (even at the participant’s request), but the treatment may be suspended upon the patient’s request or the physician’s decision.

Researchers responsible for outcome measurement will be blinded to group allocation; unblinding will not be possible for any reason.

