### 2.7. Outcomes

The outcome measures will be performed at study entry prior to randomization (T0), at the end of the training program (6 months, T1) and after the 12-month follow-up (T2).

The primary outcome measure will be the 6-min walking test [35]. Patients will be asked to walk back and forth in a standard 20-m corridor with the goal of covering as much distance as possible in 6 min. Patients will be asked to report the distance at which claudication symptoms began, which will be recorded as pain-free walking distance (PFWD). When necessary, they will be allowed to stop as needed and restart whenever possible. The total distance walked, or 6-min walking distance (6MWD), will be measured. Heart rate will be continuously measured throughout the test with a heart rate monitor, and maximal oxygen consumption may be calculated according to the published formulas. The rate of perceived exertion (RPE), according to the 1-10 Borg RPE scale, will be collected at the end of the test [36]. The minimal clinically important difference for 6MWD will be set at 36 m [37].

Secondary outcomes will include the following:

The ABI will be measured according to published standards [38]. With the patients lying in a supine position, blood pressure values at the posterior tibial and dorsalis pedis arteries will be collected, along with systolic blood pressure. The ratio of the highest value measured in each leg to the pressure measured in the arm will be used to obtain the ABI values.

The Vascular Quality of Life Questionnaire-6 (VascuQoL-6) is composed of 6 questions that assess the impact of PAD on patients’ quality of life in the previous two weeks. The scores range from 6 to 24, where a higher score corresponds to a better QoL [39].

Foot temperature will be measured with an infrared thermal camera (FlirOne Pro, Flir, Milan, Italy) at three points on the dorsum of each foot: the posterior tibial artery behind the malleolus, the anterior tibial artery at the ankle, and the dorsalis pedis artery on the dorsum of the foot.

A five-time sit-to-stand test will be used to measure lower limb strength. The patient will sit with both arms folded across his/her chest, and he/she will be asked to stand and sit five times consecutively, aiming to complete them as quickly as possible. The total elapsed time will be recorded.

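### Baseline adjustment of the walking-distance comparison is triggered by observed imbalance instead of being fixed in advance, which gives up precision at no saving

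*Protocol article*

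**What the plan says.** All of the analysis wording is in section 2.12 of the protocol article.

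- Main comparison: "Between-group differences in all outcomes according to the trial hypotheses will be tested with Student’s t-test or the Mann-Whitney U test as appropriate".
- Before that: "The distribution of the data will be assessed with the Shapiro-Wilk test". The article does not state outright that this check selects the test, but the placing of the two sentences suggests it.
- Baseline: "Between-group comparisons at baseline will be performed with Student’s t-test, the Mann-Whitney test, or the chi-squared test", chosen by the nature and distribution of the data.
- Adjustment: "In case of baseline differences between groups, appropriate adjustment measures (e.g., analysis of covariance) will be carried out". No threshold for a difference and no covariate is named.
- Missing data: "An intention-to-treat analysis will be used, with missing values replaced using the multiple imputation procedure".

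Section 2.5 describes the allocation: "Participants will be stratified by their degree of PAD severity (ankle-brachial index [ABI] > or <0.5) and the presence of diabetes", and "The randomization scheme (1:1 ratio) will be structured in permuted blocks of 8". Neither stratification factor is mentioned again in section 2.12.

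Section 2.7 has the walking test done at study entry, before randomisation, and again at 6 months, so a baseline value is planned for every patient. Section 2.8 gives 27 patients per group, 90% power and a margin of 36 m on 6MWD. Nothing says whether the 6-month value or the change from baseline is compared.

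**The concern.** In a randomised trial, baseline differences arise by chance. The reason to adjust for baseline 6MWD is that it predicts 6-month 6MWD, and that holds in every trial, balanced or not. A rule that adjusts only when an imbalance is seen therefore leaves most trials unadjusted. With a 0.05 threshold on one baseline test (an assumption, since none is stated), it would adjust in about 5% of trials. Precision that has already been paid for is left unused in a 60-patient trial.

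Three related weaknesses follow from the same wording.

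- Stratifying on prognostic factors and then using a test that ignores them overstates the standard error.
- A mean comparison and a rank comparison answer different questions. Only the first gives a difference in metres that can be set against 36 m. The standard Mann-Whitney p-value also has no estimate and standard error to combine by Rubin's rules, although multiple imputation is planned.
- With no threshold, covariate or scale named, the analyst has several admissible p-values for one comparison.

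**Working it through.** **Inputs from the article.** 27 per group, 90% power, 36 m and 10% dropout (section 2.8); significance at p < 0.05 (section 2.12).

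**Assumed.** Two-sided test; 36 m taken as the difference to detect; correlation ρ between baseline and 6-month 6MWD of 0.5 to 0.8; adjustment triggered when the baseline test gives p < 0.05. The article gives no SD, ρ or threshold.

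**1. The plan's own figure.** With no SD stated, 27 per group cannot be reproduced independently, but the SD it implies can be found:

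SD = 36 × √(27/2) / (1.960 + 1.282) = 36 × 3.674 / 3.242 = 40.8 m

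The noncentral t gives 40.0 m, and a one-sided 0.05 test would imply 45.2 m. The implied effect is 36/40.8 = 0.88 SD. The dropout step reproduces: 27/0.9 = 30 per group, 60 in total.

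**2. Adjusting in every case (normal approximation, SD 40.8 m).** Power = Φ(36 / (s × √(2/27)) − 1.96), where s is the residual SD.

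- If the unadjusted test uses 6-month values: s = 40.8 × √(1 − ρ²). At ρ = 0.5, s = 35.3 m, the standard error is 9.6 m, and power = Φ(3.74 − 1.96) = 96.3%.
- If it uses change scores with that SD: s = 40.8 × √((1 + ρ)/2).

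| ρ (assumed) | 0.5 | 0.6 | 0.7 | 0.8 |
|---|---|---|---|---|
| ANCOVA power, SD 40.8 m on 6-month values | 96.3% | 98.2% | 99.5% | >99.9% |
| Per arm for 90% | 21 | 18 | 14 | 10 |
| ANCOVA power, SD 40.8 m on change scores | 96.3% | 95.2% | 94.0% | 92.7% |
| Per arm for 90% | 21 | 22 | 23 | 25 |

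The unadjusted test has 90% power in every column by construction.

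**3. The conditional rule, by simulation.** 27 per arm, bivariate normal data, SD set so that the unadjusted t-test has 90% power, ρ from 0.5 to 0.8.

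| Scale compared | ANCOVA only if baseline p < 0.05 | ANCOVA always |
|---|---|---|
| 6-month values | 91-92% | 96-100% |
| Change scores | 90-91% | 92-96% |

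On either scale the rule sits within about 2 points of the unadjusted test.

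**4. Type I error of the conditional rule.** About 4.4% down to 2.9% on 6-month values as ρ rises, and about 4.5% on change scores. Both are below 5%, because the trials that get adjusted are those in which a chance imbalance could have produced a false positive.

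**5. Strata.** In simulations with stratified blocks of 8 and prognostic strata (40% prevalence assumed for each factor), the unadjusted t-test on 6-month values rejected in 2.2-4.3% of null trials, again conservative. Adding the strata to an ANCOVA that already held baseline 6MWD gave no further power, under the assumption that the strata act through baseline 6MWD. Most of the gain comes from the baseline covariate.

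**The case against.** **The loss is modest at the plan's own assumptions.** This stands. A reader might assume an effect of 0.5 SD and 6-month values and infer that the plan has about 45% power where ANCOVA would have 60-85%. The documents do not support that: section 2.8 claims 90% power, which implies about 0.88 SD, and the scale is not stated. Section 2.8 refers to variations in 6MWD in earlier studies, which points towards change scores, where the loss is smaller still; at ρ = 0.9 it is about 1 point.

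**The error rate is not compromised.** This stands too. A reader might infer that a two-stage rule inflates false positives. Here the departure is conservative.

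**The strata may be left to the analysis plan.** Partly fair. An article need not list every covariate, but the tests it does name cannot carry the strata. A calculation that ignoring them gives a true alpha of 3.9% to 1.9% would need perfect balance and strata explaining 10-30% of variance. The article gives no such figure, and blocks of 8 in four strata with 60 patients will leave some blocks incomplete.

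**Shapiro-Wilk is not literally named as the selector.** Correct; that is an inference from adjacent sentences.

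**An unseen analysis plan may settle this.** It could not do so without departing from the published text, which states a rule for when to adjust.

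**Conclusion.** The point holds as one of efficiency and pre-specification, not as a failure of validity. Making adjustment depend on observed imbalance recovers almost none of the gain available from baseline 6MWD. At the planned 90% power, the rule costs about 5 to 8 percentage points on 6-month values (91-92% against 96-100%) and about 2 to 5 on change scores (90-91% against 92-96%). These figures rest on assumed correlations of 0.5 to 0.8, a two-sided 0.05 test, 36 m as the difference to detect, and a 0.05 trigger. Both the conditional rule and the omission of the strata err towards a conservative test. The rank-test option adds a separate problem: it cannot be read against 36 m and does not pool by Rubin's rules in its standard form.

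**What to change.** First reconcile which walking distance is primary. The abstract names pain-free walking distance and 6MWD together, section 2.7 names the 6-minute walking test, and Table 2 labels pain-free distance primary and 6MWD secondary.

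If 6MWD is confirmed, state one primary analysis: ANCOVA of 6-month 6MWD on arm, baseline 6MWD, ABI stratum and diabetes, in all randomised patients, whatever the observed baseline balance. Pool over imputations by Rubin's rules and report the adjusted mean difference in metres with its 95% CI. Remove baseline significance tests as a trigger and the normality check as a selector, and keep rank or robust methods as sensitivity analyses. If pain-free distance is primary, its own baseline value takes the place of baseline 6MWD, and the plan must say how patients who report no pain during the test are scored.

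The cost is wording only. All covariates are already collected, and the three extra terms take the residual degrees of freedom from 52 to 49 with 54 completers.

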#### 2.6.1. TiTo-SHB Group

The structured home-based TiTo walking program will be prescribed during serial visits to the hospital [21,22,23]. The program will include two 8-min sessions per day (6 days/week) of intermittent walking (1 min of exercise and 1 min of seated rest) at a prescribed speed converted into a walking cadence and followed at home using a digital metronome or a smartphone application. The walking sessions will preferably be performed overground indoors at home (e.g., in a hallway or a heated garage) to avoid the influence of weather or on a treadmill if preferred by the patient. During the trial, 3 follow-up visits (at weeks 5, 12 and 19) will be performed to evaluate patient adherence to the program and to update the exercise program, with the duration of each session remaining constant. The intensity of each walking bout will be progressively increased according to a precise scheme (Table 1). The patients will be asked to fill out a daily training record indicating completion of the exercise and any associated symptoms. Patients will be permitted to contact the rehabilitation team, composed of a physician and an exercise physiologist, by telephone throughout the study period. During the first hospital visit, a demonstrative training session will be executed with each patient.

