#### 2.6.2. Control Group

Patients randomized in this group after the baseline outcome measurement session will be advised to walk as suggested by the guidelines [1,5]. In particular, a team member will recommend that patients walk for approximately 30 min at least 3 times per week; when the patient faces claudication pain, he/she will be allowed to rest and resume walking as soon as possible. A daily log will be provided to each patient to record and compile the amount of walking performed.

All patients will undergo optimization of medical therapy by the vascular surgeon. Both interventions will last 6 months.

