### 2.8. Sample Size Calculation

Based on published data we observed the variations in 6MWD in TiTo-SHB program and in other trials including groups at usual care [20,23]. Considering a baseline mean 6MWD of 300 m, with 27 patients for each group, the study will have 90% power to confirm the superiority of TiTo-SHB respect to walking advice, with a superiority margin set at the minimal clinically important difference or 36 m [37]. Allowing for a possible 10% dropout rate during the trial, a sample size of 60 patients (30 per group) will be planned.

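### The only sensitivity analysis named, per protocol, does not test the missing-data assumption behind the multiple imputation, and its adherence filter may act unequally between arms

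*Protocol article*

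**What the plan says.** Section 2.12 fixes the primary handling of missing data: "An intention-to-treat analysis will be used, with missing values replaced using the multiple imputation procedure". It states no imputation model and no missingness assumption. It then gives the check on the result: "A sensitivity analysis (e.g., per protocol) will also be performed to test the stability of the conclusions". The per-protocol set is not defined.

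Four other places bear on this:

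- Section 2.5 rules out transfer between arms, but "the treatment may be suspended upon the patient’s request or the physician’s decision". This applies to either arm, and participants are not blinded.
- Section 2.6.1, for TiTo-SHB: "The patients will be asked to fill out a daily training record indicating completion of the exercise and any associated symptoms". In addition, "3 follow-up visits (at weeks 5, 12 and 19) will be performed to evaluate patient adherence to the program".
- Section 2.6.2, for controls: the advice is to "walk for approximately 30 min at least 3 times per week". "A daily log will be provided to each patient to record and compile the amount of walking performed". No visit to review the log is described.
- Section 2.8: "Allowing for a possible 10% dropout rate during the trial, a sample size of 60 patients (30 per group) will be planned".

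Section 2.7 schedules outcome measurement at baseline (T0), 6 months (T1) and after the 12-month follow-up (T2). It lists no walking test between T0 and T1.

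**The concern.** A sensitivity analysis of an imputed result should ask whether the conclusion survives if patients with missing values did better or worse than the imputation supposes. Per protocol asks a different question. A patient who stopped and has no T1 value is filled in by the primary analysis and removed by the per-protocol analysis. Under ordinary missing-at-random imputation within arm, both then describe the arm by its observed patients, and neither considers that the missing patient may have fared differently. With no walking test between T0 and T1, the imputation has little outcome information on how such a patient was doing.

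The per-protocol set has a second weakness. TiTo-SHB adherence can be judged against a weekly scheme (Table 1), a daily record and three visits. Control adherence can be judged against general advice and a self-kept log. Exclusions may therefore fall unequally on the two arms, and the comparison loses the protection of randomisation.

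At stake is the robustness statement. Agreement between the two analyses could be reported as stability although dropout related to outcome was never examined.

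**Working it through.** **The plan's own figure.** From 27 evaluable patients per arm and 10% dropout (2.8): 27 / (1 − 0.10) = 30 per arm, 60 in total. This reproduces. About 3 of 30 patients per arm are therefore expected to have an imputed T1 value.

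**Bias of the imputation.** Let p be the fraction missing in an arm, m the mean of its observed patients, and δ the amount by which its missing patients fall short of m. The arm's true mean is (1 − p)m + p(m − δ) = m − pδ. Within-arm missing-at-random imputation without further predictors returns m. Hence

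bias of the difference (TiTo-SHB minus control) = p_T·δ_T − p_C·δ_C.

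The documents give p (10%) but not δ. As an assumption, let δ = G, the full gain of an adherent TiTo-SHB patient over control, with G = 36 m borrowed from the margin in 2.8:

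- Only TiTo-SHB dropouts lose the benefit: 0.1 × 36 = +3.6 m (+6 m at G = 60 m).
- Equal shortfall in both arms: 3.6 − 3.6 = 0.
- Only control dropouts do worse, by 36 m: −3.6 m.

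In the first case nobody else is excluded, so per protocol also returns G, while the truth is 27/30 × G = 0.9G. The two analyses agree exactly and share the same error.

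**Per protocol under other patterns.** The illustrations below take adherent TiTo-SHB patients at +36 m and adherent controls at 0 m. All rates other than 10% dropout, and all effects, are assumptions. Truth is the mean over everyone randomised, imputed is the mean over those observed, and per protocol is the mean over those observed and adherent. Entries are differences in metres.

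| Pattern | Truth | Imputed | Per protocol |
|---|---|---|---|
| A. 10% missing per arm; missing TiTo-SHB gain 0; a further 10% of TiTo-SHB suspend, are measured and gain 0 | 0.8 × 36 = 28.8 | 28.8/0.9 = 32.0 | 36.0 |
| B. As A, but 20% missing in TiTo-SHB, 5% in control | 0.7 × 36 = 25.2 | 25.2/0.8 = 31.5 | 36.0 |
| C. 10% missing and 10% non-adherent in both arms, each 36 m worse | 28.8 + 7.2 = 36.0 | 32.0 + 4.0 = 36.0 | 36.0 |
| D. 20% of controls missing and 36 m worse; TiTo-SHB 5% missing and 10% suspended, gain 0 | 30.6 + 7.2 = 37.8 | 30.6/0.95 = 32.2 | 36.0 |
| E. As D, plus 20% of controls measured but non-adherent, 36 m worse | 30.6 + 14.4 = 45.0 | 32.2 + 7.2/0.8 = 41.2 | 36.0 |
| F. 10% missing per arm; missing TiTo-SHB keep the full gain; 10% of TiTo-SHB suspend, gain 0 | 0.9 × 36 = 32.4 | 28.8/0.9 = 32.0 | 36.0 |

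Error of the imputed result: A +3.2, B +6.3, C 0, D −5.6, E −3.8, F −0.4 m. Error of per protocol: A +7.2, B +10.8, C 0, D −1.8, E −9.0, F +3.6 m.

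The two errors share a sign in A, B, D and E, towards TiTo-SHB in the first pair and against it in the second. Both are nil in C. In F the imputation is nearly right and per protocol is not. Neither agreement nor disagreement between the two analyses reveals which pattern holds.

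**The case against.** The strongest reply is that little is fixed here. Per protocol is only an example, other checks remain open, and an imputation model, departures from it and a per-protocol definition commonly belong in an analysis plan that is not shown. That stands, and the absence of those details is not the point. The point is that the one example chosen to show stability cannot do so for the imputed values.

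Three stronger readings are tempting, and the documents do not support them.

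- A reader might infer that both analyses favour TiTo-SHB. Section 2.5 allows suspension in either arm, nothing says that TiTo-SHB patients will stop for lack of benefit, and patterns C to F give other results.
- A reader might infer that adherence is known in one arm only. Controls keep a log too, and only the review visits are one-sided. That exclusions would fall mainly on TiTo-SHB is a prediction.
- A reader might infer an overstatement of 43% by per protocol. With 3 missing and 6 measured non-adherent TiTo-SHB patients all gaining nothing, the truth is 21/30 = 0.70G, imputation gives 21/27 = 0.78G and per protocol gives G, so G/0.70G = 1.43. The arithmetic is right, but the 20% non-adherence, the zero gain and the absence of matching exclusions in controls are all assumed. In that case the primary analysis is off by only about 0.08G.

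It is also fair that 2.5 suspends treatment and not follow-up, and that 2.12 commits to intention to treat and to minimising missing values. Measuring suspended patients at T1 is therefore consistent with the plan and only needs saying.

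**Conclusion.** The point holds in a limited form. Per protocol, as named in 2.12, does not vary the assumption behind the imputation, so its agreement with the primary result is no evidence of robustness to informative dropout. This needs no assumption about direction. That its adherence filter may act unequally follows from the review visits in 2.6.1, which have no counterpart in 2.6.2.

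The size is modest. At 10% dropout the primary estimate is off by 0.1G if only TiTo-SHB dropouts lose the benefit: 3.6 m at G = 36 m, a tenth of the margin. This rests on within-arm missing-at-random imputation with no off-treatment data, which the article neither states nor excludes. The error is nil with symmetric loss and negative if worse controls drop out. The finding concerns the value of the check. It does not show that the primary result will be biased towards TiTo-SHB.

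**What to change.** In 2.12, name as the stability check a sensitivity analysis of the imputation itself: a delta-adjusted (tipping-point) analysis that shifts the imputed T1 6-minute walking distances in fixed steps, separately in each arm, and reports the combinations at which the conclusion changes. Varying both arms matters, because shifting TiTo-SHB alone would build in a direction that the documents do not establish. With 3 of 30 values imputed, each 10 m step in one arm moves the estimated difference by 3/30 × 10 = 1 m, so the grid is easy to read. Imputing missing TiTo-SHB values from the control arm can be added as an option.

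Keep per protocol only as a supplementary analysis.

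In 2.5 or 2.12, state that a patient who suspends treatment remains in the study, is measured at the scheduled T1 visit, and enters the intention-to-treat analysis with the observed value.

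The cost is a few sentences and a little more analysis on imputations already planned. No visit is added, since T1 is already scheduled for everyone. The downside is that the robustness statement may turn out less favourable.
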